#### Who delivers the intervention?

It is designed to be delivered by trained RSE teachers.

#### How, modes of delivery

*If I Were Jack* can be delivered either over four 50–60 min lessons or over six 35–45 min lessons and consists of a combination of classroom-based activities (mainly group discussion) having first viewed the IVD, in addition to pupils being asked to engage in two homework activities (one of which involves discussion with parents/guardians). Adherence to the intervention protocol will be determined as part of our process evaluation.

#### Where, locations where intervention has occurred

The intervention has been delivered in NI^43^ and Ireland, using a further locally produced IVD for Ireland. A version of the intervention, the IVD only, has been delivered in schools in South Australia.

### Outcomes

#### Primary outcome

In this trial, a reduction in unintended teenage pregnancy rates would be the ideal primary outcome measure, but the sample size would need to be very large to detect change in unintended pregnancy rates. We will therefore use a surrogate measure associated with unintended teenage pregnancy: unprotected sex at last sexual encounter, as defined by sexual intercourse without use of contraception (barrier or hormonal). Unprotected sex during teenage years is well established as the main proximate behavioural determinant of teenage pregnancy and is a commonly measured behavioural outcome in studies examining the impact of RSE interventions on teenage pregnancy.^10 12 14 50 63–65^ Studies indicate that, although other behavioural determinants (such as frequency of sexual intercourse and number of sexual partners) are important, avoidance of unprotected sex via consistent use of contraception is central in explaining variation in levels of teenage pregnancy.^18 51^ The primary outcome will be based on contraception use at last sexual intercourse (ie, answers to the question "Did you use any form of contraception the last time you had sex?”), consistent with the data on which the sample size calculation was based.^48^ An additional item will also be included related to lifetime incidence of unprotected sex in order to account for sporadic use of contraception that may not be reflected in the last sexual encounter. Participants reporting the use of natural family planning or withdrawal methods will be categorised as having engaged in unprotected sex due to the reduced efficacy of these methods in preventing pregnancy and transmission of sexually transmitted infections (STIs). This study will not undertake any data linkage with Health and Social Care or National Health Service records, given that data on conception rates are not available in NI and that data for sexual health-related services in England are not readily available as part of routinely collected data given patient privacy requirements.

#### Secondary outcomes

Secondary outcomes are 12-month impacts on knowledge, attitudes, skills and intentions to avoiding teenage pregnancy. Secondary outcomes informed by our theory of change (figure 3) include knowledge, attitudes, communication skills and intentions relating to avoiding teenage pregnancy at follow-up and are hypothesised to lead to increased intention to avoid unprotected sex. Data will be collected using a number of standardised measures, including comfort communicating about pregnancy and comfort communicating about contraception derived from mathtech behaviour inventory^65^; the male role attitudes scale^66^; sexual socialisation instrument^67^ and sexual self-efficacy scale.^68^ We will also collect data using an ‘intentions to avoid a teenage pregnancy scale’, developed and psychometrically tested in our feasibility trial.^43^ The measures were selected because the constructs they measure map closely to the theoretical framework underpinning the intervention and the reliability and completion rates of the measures were satisfactory in the feasibility trial.^43^ In addition, to assist with the economic evaluation, supplementary secondary outcomes include: frequency of engagement in sexual intercourse, contraception use, diagnosis of STIs and incidence of pregnancy and pregnancy outcomes. The collection of these data was also shown to be feasible in the feasibility trial. Finally, we will collect important individual level demographic and socioeconomic characteristics of the sample to deepen understandings of how these factors moderate effectiveness.

### Data collection

Participating pupils will be in the study for approximately 18 months and asked to complete a paper-based questionnaire during one RSE lesson at baseline and again between 12 and 14 months later. A fieldworker will administer questionnaires to pupils, under exam conditions, 2 weeks prior to commencement of intervention delivery. Informed by the process evaluation conducted in the feasibility study,^43^ teachers will be asked to stay at the front of the classroom to maintain order while alleviating any concerns that teachers may be able to see pupils’ answers. Additional fieldworkers will be available to provide support to pupils who require extra help and to ensure questionnaires are completed confidentially.

### Primary outcome

#### Process evaluation

Informed by realist approaches to the evaluation of interventions,^42 69 70^ the process evaluation has four aims. First, we will examine reasons for school participation and non-participation to inform risk of bias in the trial as well as long-term sustainability of implementation of the intervention. Second, we will examine intervention delivery and fidelity in the context of overall RSE provision in intervention schools. Third, we will assess provision in control schools and potential contamination caused by any changes to provision that could be due to participation in the trial. Fourth, we will explore self-reported perceptions of effectiveness and moderating influences in intervention schools among a sample of pupils, teachers and school principals and parents. Triangulated data collection methods will include semi-structured interviews with teachers, focus group discussions with pupils, observations of a sample of lessons and a survey of parents/guardians with follow-up focus groups. For detail on our approach to integration of the process evaluation with the experimental design methodology to achieve research objectives, see figure 4.

**Figure 4 F4:**
[figure not shown]
Integration of process evaluation with experimental design methodology to achieve research objectives. SES, socioeconomic status.

##### All schools

The school-assigned trial champion or a suitable person identified by the trial champion will complete a school background questionnaire, designed to detail more general information pertinent to trial implementation, that is, school experience of teenage pregnancy, school holidays/closures, school experience of pupils/parents or guardians who do not speak English as a first language or who do not understand English at all and school involvement in other research. An appropriate member of staff identified by the school-assigned trial champion will also complete a questionnaire about current RSE provision in the school to gain a better understanding of the nature, quantity and quality of RSE currently taught within the school as well as the facilitators and barriers to current RSE provision within the school. A school administrator will be asked to fill out a school administrator resource use record detailing associated costs (ie, postage of parent/guardian information) and time spent. Schools will be reimbursed up to the value of £100 for these costs.

##### Intervention schools

*Parent/guardian online survey*: parents/guardians will have been made aware when they were in receipt of the parents’/guardians’ information sheet that there would be an opportunity for them to respond to a short online parent/guardian survey. Eligible parents/guardians (who have not opted out of providing consent for their child to participate) will receive the link to this survey (hosted using the SurveyMonkey UK platform) in an email and/or text message issued by the school administrator inviting them to participate (postintervention delivery). The survey will ask parents/guardians about their engagement with and opinion of the parent/guardian animations and homework session and whether their child has discussed with them their experience of engaging with *If I Were Jack*. The questionnaire will be translated where possible and where necessary.

*Teacher implementation log*: teachers responsible for delivering the intervention will be asked to complete an implementation log to detail what activities were completed or not completed during each lesson, and perception of pupil engagement with each activity.

*Telephone interviews*: 15–30 min telephone interviews will be conducted by trial coordinators with school principals or trial champions in intervention schools that are not ‘case study schools’ (see below) to determine any barriers or facilitators of engagement with the intervention.

##### Case study schools

Participating intervention schools will be randomly rank ordered in each country and two case study schools from each country will be randomly selected by NICTU to participate in the process evaluation. Should a school refuse participation, a further random selection will be made.

*Observations*: country-specific trial coordinators will conduct structured observations of one randomly selected lesson in every class group in receipt of the intervention in the eight case study schools. Observations will be focused primarily on measuring teacher fidelity to implementation protocol and pupil engagement.

*Focus groups*: trial coordinators will conduct three 60 min focus group discussions in each of the eight case study schools. One group will be composed of all teachers who delivered the intervention. The second group will include a maximum of six English-speaking pupils who received the intervention. Teachers who delivered the intervention will ask for a mixture of male and female pupil volunteers and pass details of those pupils to the trial coordinator. In the event that more pupils volunteer than are needed (per school), a random selection will be made. The third group will be a maximum of six English-speaking parents/guardians (of children who received the intervention). Discussions will focus on perceived barriers and facilitators of successful implementation and engagement with different components of the intervention.

##### Fieldworkers

Fieldworkers will complete a fieldworker perception form after each visit to a school, asking them to detail what worked well and what did not in relation to data collection and any other relevant observations they may have.

##### Education/policy specialists

Trial coordinators will conduct telephone or face-to-face interviews with one or two education/policy specialists in each country. Interviews will focus on the current context of RSE policy and perceptions of how this might influence the uptake of the *If I Were Jack* intervention.

### Economic evaluation

The economic evaluation will aim to describe the costs and consequences of implementing *If I Were Jack* in UK schools so as to provide information to decision makers on the implications of potential further roll-out of the intervention. This will include the duration of time taken up by *If I Were Jack* in school from the perspective of the teacher and impact on time spent on other important curricula activities compared with time spent on standard RSE. The aim of this will be to provide a measure of the opportunity cost to schools of implementing *If I Were Jack* compared with current RSE. The structure of the evaluation will follow the National Institute for Health and Care Excellence (NICE) guidance for evaluating public health interventions^71^ and recent guidance published by Edwards *et al*
72 on economic evaluations in public health. Costs will include the cost of implementing the intervention in schools including any training involved and the cost of current RSE in the control schools. We will also collect information on healthcare cost information in the intervention and control arms including the costs of sexual health-related primary care attendances, costs associated with STIs and unintended pregnancies (although numbers of these are likely to be small). The cost of adapting *If I Were Jack* to different groups will also be reported given that others may want to adapt the intervention before rolling it out. Mean cost per pupil will be reported alongside consequences including use of contraception, STIs and unintended pregnancies collected using questionnaires administered to pupils at baseline and follow-up. Although 12–14 months recall time is a relatively long time period, pupils are likely to be able to recall high impact events that occurred during this period. The follow-up time is also important to fit within the school year timetable. Costs will also be reported by country, given the different sexual health services provided and hence differential implications for health service costs by country.

Given that STIs and unintended pregnancies are likely to be rare but potentially high impact events in this population group, the long-term costs and consequences will be modelled as part of the cost-effectiveness decision model (figure 5), incorporating theories of behaviour change and identified as applicable for use in this trial during the feasibility trial.^45^ In addition to collecting information as part of the trial, we will look to systematic reviews of evidence of the impact of digital interventions on sexual health behaviour in this population group, for example, the review recently undertaken and published by Bailey *et al*.^73^ We will undertake one-way, two-way and probabilistic sensitivity analyses of the results. Cost-effectiveness acceptability curves and cost-effectiveness planes will be reported. The model will have a 20-year time horizon and discounting of future costs and benefits will comply with NICE guidance for evaluating public health interventions.^71^

**Figure 5 F5:**
[figure not shown]
Current and future impacts of *If I Were Jack* on costs and benefits. STI, sexually transmitted infection.

### Statistical methods

The reporting and presentation of findings will be in accordance with the Consolidated Standards of Reporting Trials (CONSORT) guidelines for cRCTs.^74^ All analyses will take account of clustering by school using robust SEs, and intervention and control groups will be compared at baseline via frequencies/descriptive statistics (percentage, mean or median as appropriate) in relation to sex, ethnicity, SES at school level (using %FSM and postcode data) and at individual level (using highest education qualifications of parents), primary and secondary outcomes.

Primary analysis (12–14 months follow-up): the primary effectiveness analysis will be on an intention-to-treat basis, using a multilevel logistic regression model (two levels: pupils nested within schools) adjusting for the baseline outcome and stratification variables.^75^ Sensitivity analyses, making different assumptions on the best and worst case scenarios, as well as imputation models of missingness will be conducted to investigate the potential impact of missing data.

Secondary analysis (12–14 months follow-up): although the trial is not powered to detect the influence of mediating and moderating variables, we will examine the following outcomes informed by our theory of change model (figure 3): (i) interaction terms will be used to investigate possible differences in the effect of the intervention on the primary outcome by whether pupils at baseline reported having had unprotected sex or not, country (Wales, England, Scotland, NI), sex, socioeconomic group (see earlier section 5.5) and ethnicity); (ii) a mediational analysis, using an analytic framework recommended for RCTs,^76^ will be used to explore whether the effect of the intervention on the primary outcome is mediated by individual-level sexual health knowledge and sexual competence, perceived behavioural control, intentions to avoid an unintended pregnancy, communication with parents and gender ideologies. In these secondary analyses, p values will be interpreted with caution due to the low power and number of interactions being tested (eg, use of Bonferroni corrected p values).

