### Sample size

The sample size calculation is based on UK-wide data^48 49^ demonstrating that between 25% and 33% of 15 years old are having sex and the proportion of 15 years old reporting unprotected sex is 2.8% (overall in NI, England, Scotland and Wales). The study will be powered to detect a 50% reduction in the incidence of unprotected sex (from expected rate of 2.8% to 1.4%) by 15 years of age. Such a difference of 1.4% in unprotected sex has been shown to have a meaningful impact on pregnancy rates.^14 50–52^ The between-group difference in the incidence of unprotected sex of 1.3% (95% CI 0.5% to 2.2%) by 9 months in our feasibility trial^43^ demonstrates that such an effect size is plausible and is consistent with effect sizes seen in the literature.^50^ The study will take account of clustering. In the feasibility data, the intraclass correlation coefficient (ICC) was 0.01.^43^ As pilot studies can provide imprecise estimates of ICCs,^53^ we re-estimated using ICCs from three sources, the RIPPLE cRCT,^52^ a 2013/2014 WHO Health Behaviour in School-aged Children survey^48^ and a 2013 Young Persons’ Behaviour and Attitudes Survey in NI conducted by the Northern Ireland Statistics & Research Agency (NISRA).^49^ The data from WHO and NISRA studies were combined. The Randomised Intervention of a PuPil-led sex education trial (RIPPLE) and combined WHO and NISRA studies found an ICC of 0.004. Assuming 120 students per school, an ICC of 0.01% and 7% attrition (plus two additional schools to be conservative), a trial involving 33 schools per group will provide 80% power at a 5% significance level (a pupil participant sample size of n=7904, with n=224 reporting unprotected sex). The power would rise to 93% if the ICC is 0.004.

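### The only pupil-level covariate in the primary model is a rare yes/no that merges pupils who have never had sex with sexually active, protected pupils; three levels would use the same data better

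*Protocol article*

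**What the plan says.** - **Model.** Under Statistical methods, the primary analysis is by intention to treat. It uses a multilevel logistic regression (pupils within schools) "adjusting for the baseline outcome and stratification variables". The Randomisation section defines the strata: two %FSM levels within each of four countries.
- **Outcome.** Under Primary outcome, it is unprotected sex at last intercourse. Withdrawal and natural family planning count as unprotected.
- **Rates.** Under Sample size, 25–33% of 15-year-olds are having sex and "the proportion of 15 years old reporting unprotected sex is 2.8"%. Mean age at baseline is 14 (Eligibility criteria for participants). No baseline rate of sex or of unprotected sex is given.
- **Data at hand.** The supplementary secondary outcomes include "frequency of engagement in sexual intercourse, contraception use, diagnosis of STIs". Under Statistical methods, the groups are compared at baseline "in relation to sex, ethnicity, SES at school level", and on the primary and secondary outcomes. The Economic evaluation section says contraception use is asked at baseline and follow-up. The randomisation code is released only after baseline data collection is complete.
- **Power.** The stated inputs under Sample size read "Assuming 120 students per school, an ICC of 0.01% and 7% attrition (plus two additional schools to be conservative". On these, the section claims that "a trial involving 33 schools per group will provide 80% power at a 5% significance level". It puts power at 93% for an ICC of 0.004.

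**The concern.** Sexual experience at baseline is the obvious predictor of unprotected sex a year later. The planned covariate keeps only a small part of it. A pupil coded no at baseline may never have had sex or may be sexually active with contraception, and their risks over the following year are likely to differ widely. A yes should be uncommon at mean age 14, so the covariate can explain little.

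What is at stake is precision, not validity. At an ICC of 0.01, about half of the variance of the treatment effect lies between schools. Schools probably differ in how sexually active their pupils are. A covariate that records experience can remove part of that variation, and chance imbalance in it, where the binary code cannot.

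**Working it through.** **1. Reproducing the plan's figure.** The effect is "from expected rate of 2.8% to 1.4"%, tested two-sided at 5% (two-sided is assumed). The ICC is printed as 0.01% in the power sentence. I read it as 0.01 because the feasibility data are reported as "the intraclass correlation coefficient (ICC) was 0.01", and because 0.01% would need only about 15 schools per group.

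- Pupils per arm without clustering, two proportions, no continuity correction: 1,646.
- Analysed per school: 120 × 0.93 = 111.6.
- Design effect: 1 + (111.6 − 1) × 0.01 = 2.106.
- Schools per group: 1,646 × 2.106 / 111.6 = 31.06, so about 31, plus two = 33.
- Power at ICC 0.01: 79.9% with 31 schools and 82.3% with 33. At ICC 0.004: 92.3% and 93.7%.

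The stated 80% and 93% reproduce, with no credit taken for covariates.

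**2. What the binary code hides.** At the age-15 figures, 2.8/33 = 8.5% to 2.8/25 = 11.2% of sexually active pupils would be coded yes. The other 89–92% share a code with pupils who have never had sex.

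**3. Where the variance lies.** The between-school share is m × ICC / design effect.

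- ICC 0.01: 1.116/2.106 = 53%.
- ICC 0.004: 0.446/1.442 = 31%.

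**4. Formula check.** Let R²w and R²b be the shares of within-school and between-school variance that the covariates remove. The adjusted design effect is (1 − R²w)(1 − ICC) + (1 − R²b) × 111.6 × ICC. With 33 schools per group:

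- ICC 0.01, R²w 0.01–0.05, R²b 0: 82.3% rises to 82.5–83.2%.
- ICC 0.01, same R²w, R²b 0.1–0.3: 84.5–89.2%.
- ICC 0.004, same R²w, R²b 0.1–0.3: 93.7% rises to 94.5–96.2%.

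Any material gain must therefore come from between-school variance.

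**5. Simulation.** 66 schools of 112 analysed pupils in the eight strata; 2.8% v 1.4%; logistic models with school-robust standard errors; strata in every model; 800 runs per row (simulation SE about 1 point per figure; the models share the same data). All baseline inputs are assumptions. Odds are relative to pupils who have never had sex, and 7–10% of experienced pupils are taken as unprotected. A school SD of 0.57 on the log-odds scale gives an ICC of about 0.028 × 0.57² / 0.972 = 0.009; an SD of 0.35 gives about 0.004. The correlation is between a school's outcome effect and its baseline activity.

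| Experienced at baseline | Odds, protected / unprotected | School SD | Correlation | Planned model | Three levels | Gain |
|---|---|---|---|---|---|---|
| 10% | 3 / 6 | 0.57 | 0.5 | 85.1% | 88.4% | 3.3 |
| 10% | 5 / 8 | 0.57 | 0.7 | 83.1% | 88.9% | 5.8 |
| 5% | 3 / 6 | 0.57 | 0.5 | 84.4% | 86.5% | 2.1 |
| 10% | 5 / 8 | 0.35 | 0.7 | 95.9% | 97.6% | 1.8 |
| 10% | 3 / 8 | 0.57 | 0 | 85.8% | 86.5% | 0.8 |
| 15% (extreme) | 8 / 12 | 0.57 | 0.9 | 77.9% | 90.4% | 12.5 |

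A separate set of simulations, also with strata in every model, put the gain from the three-level variable at roughly 0.5 to 7 points, with null rejection near 5%. Adding the binary baseline outcome to a strata-only model gained only 0.3 to 1.6 points.

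**6. Further covariates.** On top of three levels, pupil sex changed power by 0.3 points or less in every row. The school's baseline proportion sexually experienced then added 1 to 6 points where school effects were correlated and the school variance was at the planned level. It lost about 0.5 points in the zero-correlation and small-variance rows.

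**The case against.** The strongest reply is that nothing here is wrong. The model is coherent, prespecified and valid; the sample size claims no benefit from covariates; and the power reproduces. That stands, and it sets the weight of the point.

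It is also fair that the gain rests on inputs the protocol does not give. The link between school effects and baseline activity decides the answer, and without it the gain is within simulation error. At an ICC of 0.004, the value the protocol reports from its larger external sources, less remains to be gained. The simulations used school-robust standard errors and not the planned multilevel fit, so the differences between models are more reliable than the absolute powers. These limits stand.

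Two practical objections carry less weight. Missing data: deriving the planned covariate already requires knowing whether the pupil has had sex and whether contraception was used, so three levels should add little or no missingness. Change of estimand: another covariate alters the conditional odds ratio, but the planned model is already conditional on covariates and school.

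A reader might infer more than the protocol supports:

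- **That the model adjusts for the baseline outcome alone.** It also adjusts for the strata, and the recruitment section links deprivation to unprotected sex.
- **That the baseline outcome is known to be almost empty.** This is inferred from age; no baseline rate is given.
- **That pupil sex and the school's baseline rate should be added at no cost.** Sex contributed nothing useful. The school rate is noisy at about 120 pupils (reliability about 0.55 at ICC 0.01 and 0.33 at 0.004), uses a between-school degree of freedom and can slightly lower power. One null check with it rejected in 7.5% of 400 runs (simulation SE about 1.1 points). That is too few runs to prove inflation, but it does not support calling the term free.

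**Conclusion.** The point holds as an efficiency improvement, not as an error and not as a power shortfall. The only pupil-level covariate discards most of the baseline information on sexual experience that the trial will already hold.

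With 5–10% of pupils experienced at baseline, three levels in place of two add about 0–7 power points at an ICC near 0.01 and less at 0.004 (1.8 points in the row nearest that value). The low end applies if school effects are unrelated to baseline activity. The larger gain in the 15% row depends on extreme assumptions and should not be relied on. No loss beyond simulation error appeared in any scenario.

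For scale, the two schools added as a margin are worth 82.3 − 79.9 = 2.4 points.

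**What to change.** In the primary analysis paragraph, replace the baseline outcome by baseline sexual experience in three levels: never had sex, last sex protected, last sex unprotected. Use the same definition of unprotected as for the primary outcome. Keep country and %FSM stratum. The third level is the planned covariate's yes group, so no new sparse category is created, and the planned interaction with baseline unprotected sex can stay as it is.

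The cost is one sentence and one extra parameter. At the design rates, 7,904 × 2.1% × 0.93 gives about 154 expected events to support it. No new data are needed. The change should be fixed before outcome data are examined by group.

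Do not add pupil sex on grounds of power. If the school's baseline proportion sexually experienced is of interest, prespecify it as a sensitivity analysis only.

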## Introduction

Teenage pregnancy remains a worldwide health concern and is both an outcome of, and contributor to, inequalities in health.^1^ The UK has the highest rate of teenage pregnancy in Western Europe.^2^ While conception rates for girls aged under 18 years have halved since 1998 in England and Wales, and now stand at 21.0 per 1000 population,^3^ it remains that just over 20 000 teenage women under 18 years became pregnant in England and Wales in 2015 and approximately half of these ended in legal abortion.^3^ The conception rate for Scotland was 32.4 per 1000 in 2015.^4^ In Northern Ireland (NI), abortion is illegal and is only considered lawful in exceptional circumstances where the life of the pregnant woman is at immediate risk or if there is a risk of serious injury to her physical or mental health. Reflecting this different legal framework, government targets around reducing teenage pregnancies in NI relate to births and not conceptions. In NI, the birth rate for teenage mothers per 1000 young women aged 13–19 years was 11.3 in 2013.^5^ In the same year, the teenage birth rate in the most deprived areas was 23.0 per 1000, nearly six times that of the least deprived areas in NI (3.9 per 1000).^6^

Although the life course for teenage parents is not universally negative,^7^ the social disadvantage and exclusion that are linked to teenage pregnancy are considered problematic.^1^ Unintended teenage pregnancy can lead to considerable adverse health problems for teenagers and their infants as well as generating emotional, social and economic costs for them, their families and society.^8 9^ While unintended teenage pregnancy is a complex phenomenon that cannot be prevented through relationship and sexuality education (RSE) alone,^10–16^ high-quality RSE is an essential component in the process of reducing unintended pregnancy rates, as well as being a vital aspect of improving holistic sexual health and well-being.^17–21^ The UK governments all emphasise the policy importance of decreasing under-18 conception rates and increasing sexual health precaution behaviours in teenagers via the implementation of RSE in schools as a key objective in their current sexual health policies.^22–24^

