### Recruitment and retention

#### Recruitment of schools

In each country, eligible schools will be stratified based on the percentage of students eligible for free school meals (%FSM) for the 2018/2019 academic year (schools above and below the median national %FSM) as a proxy for the level of deprivation. In NI, 14 schools will be randomly selected from the above-median stratum and 10 from the below-median stratum (total 24). In England, Scotland and Wales, 8 schools will be randomly selected from the above-median stratum and 6 from the below-median stratum (to give a total of 14). The decision to select slightly more schools from the above-median %FSM reflects research which indicates that teenage pregnancy and unprotected sex is more acute in more deprived areas.^1 48^

The school recruitment period will run from February to June 2018. The school recruitment strategy is represented in figure 2. In Scotland, it is required that permission is given from each local authority (typically by approaching the Director of Education) prior to commencing recruitment. Any schools that decline to participate will be replaced by a randomly selected school in the same stratum.

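### The primary model could use each school's exact %FSM as well as its above/below-median class: a cheap gain in precision, not an error in a valid plan

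*Protocol article*

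**What the plan says.** The Statistical methods section sets a two-level logistic model (pupils within schools), by intention to treat, "adjusting for the baseline outcome and stratification variables". The stratification variables are defined elsewhere. Recruitment of schools divides each country's schools into two classes, "schools above and below the median national %FSM". Randomisation uses eight schedules, one per %FSM class in each country. Nothing in the article enters %FSM as a continuous value, and nothing states the coding outright.

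Two further statements bear on the point. Recruitment of schools justifies taking more schools from the above-median class because "teenage pregnancy and unprotected sex is more acute in more deprived areas". Statistical methods also lists %FSM as a school-level measure for the baseline comparison, so the value will be in the trial data.

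**The concern.** A median split gives the same code to a school just above the median and to the most deprived school in the country. If risk rises with deprivation inside each class, that part of the between-school variation stays in the model's error although the trial holds the figure that would explain it. The protocol gives reason to expect some gradient. Besides the statement on unprotected sex, the Introduction reports NI teenage birth rates of 23.0 against 3.9 per 1000, "nearly six times that of the least deprived areas in NI".

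Between-school variation is also the expensive part of this design. At the planning ICC of 0.01 it accounts for about half of the variance of the effect estimate. Strata are small: from the recruitment numbers (14 and 10 schools in NI, 8 and 6 elsewhere), a balanced allocation puts only 3 to 7 schools per arm in each stratum. Chance differences in deprivation within strata are therefore likely, and the two-level term cannot adjust for them. At stake is some precision, not validity.

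**Working it through.** **Inputs from the Sample size section**
- Outcome rate falling "from expected rate of 2.8% to 1.4" per cent; 5% significance level, taken as two-sided.
- "Assuming 120 students per school, an ICC of 0.01% and 7% attrition (plus two additional schools to be conservative". The ICC is read as 0.01, because the same section says that in the feasibility data "the intraclass correlation coefficient (ICC) was 0.01". A literal 0.01% would give about 99% power, not 80%.
- Alternative ICC 0.004, with stated power 93%.

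**Inputs assumed, because the documents give no figure**
- R², the share of between-school variance that exact %FSM explains: working range 0.1 to 0.5, with 0 and 1 as limits.
- A median split keeps 2/π = 0.64 of the R² of a roughly normal covariate with a linear effect.

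**Step 1: reproduce the plan's figure**
- Pooled-variance formula for two proportions: n = {[1.96 × √(2 × 0.021 × 0.979) + 0.8416 × √(0.028 × 0.972 + 0.014 × 0.986)] / 0.014}² = 1646 per arm.
- Analysed pupils per school: 120 × 0.93 = 111.6.
- Design effect: 1 + 110.6 × 0.01 = 2.106.
- Schools: 1646 × 2.106 / 111.6 = 31.06, so 32 per arm or 64 in all. Adding two gives 66, or 33 per arm.
- Pupils: 66 × 120 = 7920, against 7904 stated.
- Power at ICC 0.01: 79.9%, 81.2% and 82.3% with 31, 32 and 33 schools per arm.
- Power at ICC 0.004: 93.0% with 32 and 93.7% with 33 per arm.

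The stated 80% and 93% are reproduced, and no covariate adjustment enters them.

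**Step 2: the part that %FSM can act on**
- Share of variance due to clustering at ICC 0.01: 1.106 / 2.106 = 53%.
- At ICC 0.004: 0.442 / 1.442 = 31%.

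**Step 3: split against exact value, 33 schools per arm**
- Design effect with the split: 1 + 110.6 × ICC × (1 − 0.64 R²).
- Design effect with exact %FSM: 1 + 110.6 × ICC × (1 − R²).
- Effective n per arm is 33 × 111.6 / design effect, put into the same power formula.

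| ICC | R² | Design effect, split → exact | Variance | Power, split → exact | Gain (points) |
|---|---|---|---|---|---|
| 0.01 | 0 | 2.106 → 2.106 | 0 | 82.3% → 82.3% | 0 |
| 0.01 | 0.1 | 2.035 → 1.995 | −2.0% | 83.6% → 84.3% | 0.7 |
| 0.01 | 0.3 | 1.894 → 1.774 | −6.3% | 86.1% → 88.2% | 2.1 |
| 0.01 | 0.5 | 1.752 → 1.553 | −11.4% | 88.6% → 92.0% | 3.4 |
| 0.004 | 0.1 | 1.414 → 1.398 | −1.1% | 94.1% → 94.4% | 0.2 |
| 0.004 | 0.3 | 1.357 → 1.310 | −3.5% | 94.9% → 95.6% | 0.6 |
| 0.004 | 0.5 | 1.301 → 1.221 | −6.1% | 95.7% → 96.7% | 1.0 |

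Gains are taken from unrounded powers. At R² = 1 they are 4.4 points (ICC 0.01) and 1.4 points (ICC 0.004). If the split keeps 75% rather than 64%, the gain at ICC 0.01 for R² 0.1 to 0.5 is 0.5 to 2.3 points.

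**Step 4: check by simulation**

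66 schools in eight strata, about 112 pupils each, 6000 runs per setting, school-level linear model with arm and country in every fit. Power with split against exact value:
- ICC 0.01: 83.0% v 82.8% (R² 0), 85.0% v 86.4% (R² 0.2), 86.9% v 90.3% (R² 0.5).
- ICC 0.004: 94.2% v 94.6% (R² 0.2), 95.4% v 96.4% (R² 0.5).

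The formula and the simulation agree closely on the gain.

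**The case against.** The strongest reply is that nothing is wrong with the plan. Adjusting for the factors used to stratify randomisation is standard and valid. In a separate simulation of the two-level logistic model, null rejection was 5.4% to 6.2% under both codings. Chance imbalance within strata is not bias, because the standard error already allows for it. All of this stands.

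A second reply is that the article never states the coding, and an analysis plan that is not shown may settle it. This stands in part. The split is the natural reading of the three sections taken together, but it is a reading.

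Two stronger readings are tempting and are not supported:

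- **That the trial loses power it claims to have.** The stated power takes no credit for covariates and is reproduced without them. Any loss is relative to a better model, not to the protocol's claim.
- **That the NI birth gradient shows a large loss.** If the two birth rates are taken to lie 2.8 SD of deprivation apart, the slope is ln(23.0/3.9)/2.8 = 0.634 per SD. Simulated power then rises from 92.0% to 97.6%. But with the between-school log-risk variance of 0.466 used there, %FSM would have to explain 0.634²/0.466 = 86% of all school variation. The birth rates are by area, for young women aged 13 to 19, and the 2.8 SD is itself an assumption. For the trial's own outcome the documents give only the direction.

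The planned model also adjusts for the baseline outcome, which may already carry part of the deprivation effect. The calculation leaves this out, so the gains shown may be too large.

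**Conclusion.** The point holds as an optional improvement in efficiency. On the natural reading, the primary model uses a two-level version of a school measure that the trial holds exactly and that the protocol itself links to the outcome. The gain is modest. At ICC 0.01 and R² 0.1 to 0.5 it is worth roughly 1 to 8 extra schools (66/0.980 = 67.3; 66/0.886 = 74.5), set against the two that the plan added as a margin. At ICC 0.004 power is already about 94% and there is little left to gain.

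The size rests on an assumed R², a linear effect of %FSM, a roughly normal distribution of %FSM across schools, and no overlap with the baseline outcome. The direction is well founded; the amount cannot be established from the documents.

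**What to change.** In the primary model keep the terms for country and %FSM stratum, and add each school's %FSM as a continuous covariate, centred within country, using the value that placed the school in its stratum. Write this into the analysis plan before allocation is released. The Randomisation section has the code held until all schools are recruited and baseline data are complete, so there is room to do it without knowledge of allocation. Added later, the choice would look post hoc.

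The cost is one sentence, one degree of freedom among 66 schools, and no new data. The downside is the assumption of linearity with a common slope across countries, which keeping the stratum term softens. If %FSM has no effect within strata, the loss is negligible (83.0% v 82.8% in the simulation at ICC 0.01).
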